## Abstract

**Background:**

Diagnosis and treatment of cancer can contribute to psychological distress and anxiety amongst patients. Evidence indicates that information giving can be beneficial in reducing patient anxiety, so oncology specific information may have a major impact on this patient group. This study investigates the effects of an orientation program on levels of anxiety and self-efficacy amongst newly registered cancer patients who are about to undergo chemotherapy and/or radiation therapy in the cancer care centre of a large tertiary Australian hospital.

**Methods:**

The concept of interventions for orienting new cancer patients needs revisiting due to the dynamic health care system. Historically, most orientation programs at this cancer centre were conducted by one nurse. A randomised controlled trial has been designed to test the effectiveness of an orientation program with bundled interventions; a face-to-face program which includes introduction to the hospital facilities, introduction to the multi-disciplinary team and an overview of treatment side effects and self care strategies. The aim is to orientate patients to the cancer centre and to meet the health care team. We hypothesize that patients who receive this orientation will experience lower levels of anxiety and distress, and a higher level of self-efficacy.

**Discussion:**

An orientation program is a common health care service provided by cancer care centres for new cancer patients. Such programs aim to give information to patients at the beginning of their encounter at a cancer care centre. It is clear in the literature that interventions that aim to improve self-efficacy in patients may demonstrate potential improvement in health outcomes. Yet, evidence on the effects of orientation programs for cancer patients on self-efficacy remains scarce, particularly with respect to the use of multidisciplinary team members. This paper presents the design of a randomised controlled trial that will evaluate the effects and feasibility of a multidisciplinary orientation program for new cancer patients.

**Trial registration:**

Current Controlled Trials ACTRN12609000018213

## Background

There is a consensus that diagnosis and treatment of cancer contributes to psychological distress and anxiety among patients [1-3]. The literature has demonstrated that information can reduce distress by enhancing patients' sense of control. An enhanced sense of control, in turn, relieves anxiety and enhances management of illness [4]. Although the need for information exists across the continuum of cancer care [5,6] the anxiety can be particularly pronounced at the initial visit to a cancer centre [7,8]. Factors contributing to this anxiety and distress can be the lack of familiarity with the environment and with the care providers.

Researchers have investigated interventions with the aim of reducing the anxiety and distress levels among cancer patients [4,9]. One of these interventions includes orientation programs for patients who are newly registered to a cancer service. A study of 150 new cancer patients by McQuellon and research team reported that their orientation was effective in reducing anxiety, distress and depressive symptoms and enhanced knowledge and satisfaction of care [10]. In 2003, Gallant (2003) tested different methods of delivering an orientation program and found that it was more challenging to recruit patients for the face to face arms compared to the mail group [11]. The components of these orientation programs vary and generally include question and answer sessions, a clinic tour, description of procedures, provision of information. However, none of these studies have investigated the effects of orientation programs and were not conducted by a multidisciplinary team.

### Self-efficacy

In the population other than cancer patients, researchers have demonstrated that self-efficacy can be enhanced through orientation and educational programs, and that higher self-efficacy is related to improved health outcomes [12-15]. Self-efficacy is a construct of Bandura's social cognitive theory [16,17], defined as a person's belief that they can perform the specific behaviours necessary to achieve their goals. A person's sense of self-efficacy should lead to attempting and persisting when encountering difficulties; their confidence in or perception of their ability to carry out tasks directly relates to their likelihood of success [18]. A variety of research on cancer patients' self-efficacy has been conducted [19-23]. Self-efficacy is a potent factor which can affect the quality of life in cancer patients. Firstly, enhanced self-efficacy directly affects quality of life positively. Secondly, it reduces perceived stress and, in turn, increases quality of life [23]. That is, cancer patients with higher self-efficacy have lower level of anxiety and distress and higher quality of life [21,23,24]. Therefore, interventions with the aim of increasing ones' self-efficacy are recommended.

### Multidisciplinary team involvement

A systematic review reported that multidisciplinary care can result in positive patient outcomes [25], specifically in diagnosis and/or treatment planning [26-28], survival [29-31], patient satisfaction [26], communication and cooperation [32]. Although there is a vast body of literature supporting the positive outcomes as a result of multidisciplinary care, there is a paucity of evidence which demonstrates the importance of multidisciplinary involvement in conducting orientation programs for cancer patients. While evidence suggests that unfamiliarity with the care providers is one of the factors contributing to this anxiety and distress in this patient population [33], it is important to note that "care providers" should include every member that the patients will access care from during the continuum of cancer care. Orientation provided for cancer patients should no longer be limited to "meeting the oncologist". As the model of care has changed from a medical focus to a multidisciplinary model, health professionals conducting orientation programs should also respond to the change. However, the orientation programs documented in the literature are mainly conducted by one nurse coordinator, rather than a multidisciplinary team [10,33,34]. Therefore, research is needed to evaluate the effectiveness of an orientation program conducted by a multidisciplinary team.

### Objective of the study and the current paper

The main objectives of the study are

1. To develop an orientation program conducted by a multidisciplinary team for newly registered cancer patients in terms of its impacts on the patients' self-efficacy and anxiety.

2. To test the feasibility of a randomised controlled trial of an orientation program conducted by a multidisciplinary team for all newly registered cancer patients.

3. To evaluate the effectiveness of the program on patients' self-efficacy, anxiety, stress and informational awareness.

The current paper presents the design of the randomised controlled trial that will evaluate an orientation program conducted by a multidisciplinary team for newly registered cancer patients

## Methods

### Method

Randomised controlled trial will be used in this study.

### Ethics consideration

The study protocol has been reviewed and approved by the Royal Brisbane & Women's Hospital Health Service District Human Research Ethics Committee.

### Study population

All cancer patients newly registered at a tertiary cancer care centre in Brisbane, Australia, who meet inclusion criteria will be invited to participate in the trial. Patients who consent will be randomly allocated to either the control group, who will receive normal treatment education at the start of their treatment, or the intervention group, who will receive the normal treatment education and will also attend the Orientation Program education session conducted by the multi-disciplinary team, prior to starting their treatment.

#### Inclusion and exclusion criteria

Patients will be eligible if they consent and are undergoing a course of radiotherapy, chemotherapy or both; have a definitive diagnosis of cancer; are over 18 years of age; are able to read and write in English and are "well" enough to complete the questionnaire. Patients will be excluded if they have had previous cancer treatments.

### Randomisation and masking

Patients will be randomly allocated to either normal care (control group) with standard education provided by nurses at the first visit of treatment, or to the intervention group to participate in an extra orientation program.

#### Sequence generation

Blocked randomisation will be performed with a block size of four by a computer generated random number list prepared by an investigator who has no clinical involvement in the trial. Stratification by primary cancer diagnosis group will also be carried out.

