#### Allocation concealment/implementation

After the research nurse has obtained the patient's consent, he/she will telephone a contact who is independent of the recruitment process for allocation concealment. Subsequently, baseline data will be collected. All questionnaires are self-administered by patients. Therefore, the research nurse will not have involvement in completing these questionnaires.

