#### Blinding/masking

It is not possible to blind patients regarding the result of randomisation in this type of intervention. While it is not possible to blind the health professionals administering the orientation program, they will have no involvement in assessing and analysing the data.

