### Sample size and power

A sample size of at least 375 in each arm of the study would be sufficient to achieve a power of 90% using 95% of confidence interval to detect a difference in the anxiety and self-efficacy scores between control group and intervention group. Assuming that approximately 25% fail to consent and a further 10% will be lost to follow-up; an additional 132 in each group will be required and the final sample will require 1,014 patients. In order to evaluate the research design and process, the current proposal is for a pilot study with 10% of the final sample (ie 102 patients, 51 in each arm). According to the statistics of RBWH Cancer Care Services, 274 new cancer outpatients receiving treatment each month. Thus, the sample size proposed is achievable over a period of 12 weeks based on our conservative estimation.

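### A single fixed block size of four within diagnosis groups could make up to about a third of allocations predictable to recruiting staff who track them

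*Protocol article*

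**What the plan says.** Under Sequence generation, the protocol article fixes one block size: "Blocked randomisation will be performed with a block size of four". The list is made by an investigator with no clinical role. The same section adds: "Stratification by primary cancer diagnosis group will also be carried out". The number of diagnosis groups is not given, and no variation in block size is mentioned.

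Under Study population there is one site: "All cancer patients newly registered at a tertiary cancer care centre in Brisbane, Australia". Diagnosis group is thus the only stated stratification factor. Under Sample size and power the pilot has "102 patients, 51 in each arm", so the ratio is 1:1 and each block holds two of each arm.

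Under Allocation concealment/implementation: "After the research nurse has obtained the patient's consent, he/she will telephone a contact who is independent of the recruitment process". Baseline data are collected after that call. Under Blinding/masking: "It is not possible to blind patients regarding the result of randomisation in this type of intervention".

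**The concern.** Concealment has two parts: the next entry must be hidden, and it must not be deducible from the entries already issued. The telephone step deals with the first. A single small block size weakens the second. Once two patients of one arm have appeared in a block, the rest of that block is settled for that diagnosis group.

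Stratification gives little cover. Eligibility requires a definitive diagnosis, so a recruiter knows the next patient's group before making an approach. Earlier allocations are also easy to learn, because the nurse who recruits makes the call and attendance at the orientation session is visible.

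At stake is the decision to approach or enrol. Consent before the call protects patients who have already agreed, but not the decision about the next one. Most of the criteria under Inclusion and exclusion criteria are objective, but whether a patient is well enough for the questionnaire is a judgement. The outcomes are self-reported anxiety, mood and self-efficacy, so selection on apparent distress would act on the variables being compared.

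**Working it through.** The article gives no predictability figure, so there is none to reproduce. The inputs are a block size of 4 (Sequence generation), a 1:1 ratio (from the equal arms) and 102 pilot patients (Sample size and power). The number of strata is an assumption, varied from 1 to 15.

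**Certain allocations in one complete block.** There are C(4,2) = 6 equally likely orderings of two A and two B. An allocation is certain when only one arm has places left.

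- Positions 1 and 2: never certain, probability 0.
- Position 3: certain if the first two match (AA or BB), which happens in 2 of 6 orderings, probability 1/3.
- Position 4: always certain, probability 1.

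Expected number per block = 0 + 0 + 1/3 + 1 = 4/3. Share = (4/3)/4 = 1/3 = 33.3%.

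**Best guess.** Always name the arm with more places left. The chance of being right is 1/2 at position 1 and 2/3 at position 2. At position 3 it is (2/3)(1/2) + (1/3)(1) = 2/3, and at position 4 it is 1. The average is (0.5 + 0.667 + 0.667 + 1)/4 = 2.833/4 = 70.8%, against 50% by chance.

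**The 102-patient pilot.** If every block were complete, 102 × 1/3 = 34 allocations would be certain. Last blocks are usually incomplete, which lowers this. A last block holding r patients contributes 0, 0, 0 or 1/3 certain allocations for r = 0, 1, 2 or 3, where the one-third rule would credit 0, 1/3, 2/3 or 1. The shortfall is 0, 1/3, 2/3 or 2/3. If r is about equally likely to take each value, the mean shortfall is (5/3)/4 = 5/12 per stratum. With K strata the expected number is therefore about 34 − (5/12)K. For one stratum r is exactly 2 (102 = 25 × 4 + 2), which gives 34 − 2/3 = 33.3.

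| Equal strata (assumed) | By hand | Share by hand | Share by simulation |
|---|---|---|---|
| 1 | 33.3 | 32.7% | 32.6% |
| 4 | 32.3 | 31.7% | 31.8% |
| 6 | 31.5 | 30.9% | 30.8% |
| 8 | 30.7 | 30.1% | 30.1% |
| 10 | 29.8 | 29.2% | 29.2% |
| 15 | 27.8 | 27.2% | 27.2% |

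**Other block schemes.** Enumeration as above gives 25% certain for a fixed block of six and 20% for a fixed block of eight. Simulated as one sequence of 102 patients, blocks of 4 and 6 in random order leave about 5.5% certain, and blocks of 4, 6 and 8 about 2.4%. Both figures assume that the recruiter knows the set of sizes but not their order.

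**The case against.** The strongest reply is that predictability is a property of the list, not an established fact about the nurse. A reader might infer that the nurse can deduce one allocation in three. That needs someone who recruits to know or infer the block size, to learn the earlier allocations and to tally them by diagnosis group. The article states none of these. It does not say that the nurse is told the block size, which is open only in the sense that it is printed in a published article. It does not say in so many words that the contact reads the result back to the nurse, although that is likely. This part stands, and the point must be conditional.

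A reader might also infer that the outcomes will be biased. The article does not support that. Consent comes before the call, the contact is independent, all eligible new patients are to be invited, and patients complete the questionnaires themselves. Bias from unblinded self-report is a separate matter that would exist under any block scheme.

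It can also be said that anxiety, mood and self-efficacy are measured at recruitment (T1) and that the Analysis section adjusts for factors in substantial imbalance. This helps only in part. The T1 questionnaires follow the allocation call in an unblinded trial, so a difference at T1 could reflect selection or a reaction to the allocation. Adjustment reaches only measured factors.

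Finally, keeping block sizes from recruiters is a detail that an article may leave to the full protocol, so its absence is no fault here. The stated single size is what can fairly be criticised.

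**Conclusion.** The point holds in a conditional form. One block size of four within diagnosis groups, in an unblinded single-centre trial where the recruiter calls for the allocation, leaves up to about a third of allocations certain in advance to anyone who knows or infers the size and tracks the groups. In the pilot this is about 28 to 33 of 102 patients over an assumed 1 to 15 equal strata; 34 would require every block to be complete. Independent telephone allocation after consent does not remove this. Selection bias is possible, not demonstrated, and the route is narrow: whom to approach, and whom to judge well enough. The design is otherwise valid and the remedy is cheap, so the change should be made, but the plan does not fail without it.

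**What to change.** Under Sequence generation, replace the single block size with block sizes that vary at random within each diagnosis group, for example 4 and 6. State that the sizes are not disclosed to recruiting staff, and keep them out of the documents those staff receive. A larger fixed block is not a substitute, since a fixed six still leaves 25% certain. Varying sizes make certainty rare; they do not make every guess a coin toss.

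The cost is a regenerated computer list, best done before recruitment starts. If the pilot is already under way, make the change at the latest for the full trial of 1,014, since the pilot is there to test the design. The statistical price is small: the largest possible imbalance at the end of a stratum is half the block size, so it rises from 2 patients with blocks of four to 3 with blocks of six.

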#### Allocation concealment/implementation

After the research nurse has obtained the patient's consent, he/she will telephone a contact who is independent of the recruitment process for allocation concealment. Subsequently, baseline data will be collected. All questionnaires are self-administered by patients. Therefore, the research nurse will not have involvement in completing these questionnaires.

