### Data collection

Participants will be asked to complete a series of questionnaires at the time of recruitment (T1), on the day of first treatment (T2), and on the seventh day of treatment (T3) which will measure patients' self-efficacy (CASE) and anxiety (STAI and POMS) at the three time points. Additionally, demographic information will be collected at T1 and the EOCQ will be collected at T2 and T3.

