### Analysis

All data will be analysed according to intention-to-treat principle. Means, standard deviations will be used to summarise overall and within subgroups defined by the range of medical, sociological, and other risk factors collected at baseline. Mean scores of POMS, STAI and CASE-cancer will be compared initially across intervention and control groups using ANOVA (repeated measures) to analyse the effect between groups over time (or Friedman test if normality is not a valid assumption). Success of randomisation will then be considered by cross-tabulating trial group with the range of factors. Any found to be in substantial imbalance will be included in multivariable linear regression models, via forced entry, to adjust the crude means and these will be reported with 95% confidence intervals. Analyses will use the SPSS (Version 16) package and a generalised linear modelling framework.

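### Baseline (T1) questionnaires follow the allocation call, so T1 anxiety and self-efficacy scores can already reflect knowledge of the assigned arm

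*Protocol article*

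**What the plan says.** The Allocation concealment/implementation section of the protocol article sets out a sequence. Once consent is obtained, the research nurse acts as follows: "he/she will telephone a contact who is independent of the recruitment process for allocation concealment". The next sentence reads "Subsequently, baseline data will be collected". The section adds "All questionnaires are self-administered by patients" and concludes that the nurse therefore plays no part in filling them in.

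The Blinding/masking section states: "It is not possible to blind patients regarding the result of randomisation in this type of intervention".

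The Data collection section dates T1 to recruitment, T2 to the first treatment day and T3 to the seventh. It describes the questionnaires as ones "which will measure patients' self-efficacy (CASE) and anxiety (STAI and POMS) at the three time points". The Analysis section compares mean scores on these scales between the arms "using ANOVA (repeated measures) to analyse the effect between groups over time".

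**The concern.** A baseline score is useful because it cannot have been affected by the allocation. That is guaranteed if the score is recorded before anyone knows the arm. Here the stated order puts the T1 forms after the call that produces the arm, and the people completing them are patients the article says cannot be blinded.

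The scales ask about anxiety, mood and confidence in coping. The trial's own hypothesis is that orientation improves these, so hearing that one will, or will not, have an extra session with the multidisciplinary team could plausibly move some of them. Knowledge of the arm at T2 and T3 cannot be avoided in this design. At T1 it can.

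What is at stake is the reference point for the comparison over time. If T1 has moved in one arm, the data alone cannot separate that movement from a chance difference between the groups, so it cannot be repaired afterwards.

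**Working it through.** The article gives no figure on this point, so the check is first one of order and then of simple algebra.

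**Order of events.**

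- Allocation concealment/implementation: consent, then the allocation call, then baseline data.
- Data collection: T1 is at recruitment. This fits a time just after the call and does not place T1 before it, so it does not correct the order.
- Blinding/masking: patients are not blinded. No time of disclosure is given.
- Allocation concealment/implementation and Data collection: T1 is patient-reported, on the same three instruments as T2 and T3.
- Analysis: those scores enter a repeated-measures comparison between arms over time.

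**Safeguards offered.** There are two. The independent telephone contact protects recruitment from foreknowledge of the next allocation, which is a matter before consent. The nurse's absence from questionnaire completion limits staff influence. Neither addresses what the patient knows when answering at T1, and no section says the result is held back until T1 is done.

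**Effect on the contrast.** Score each difference, intervention minus control, so that positive favours the intervention. Let

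- δ = the difference at T1 caused by learning the arm,
- k = the share of δ still present at follow-up,
- τ = the effect of the programme itself at follow-up.

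Expected difference at T1 = δ. Expected difference at follow-up = τ + kδ.

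Group-by-time contrast = (τ + kδ) − δ = τ − (1 − k)δ.

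The bias is therefore −(1 − k)δ:

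- k = 1 (reaction carries forward equally): bias 0.
- k = 0 (reaction gone by follow-up): bias −δ.
- T1 completed before allocation: δ = 0, so no bias whatever k is.

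A positive δ (relief in the intervention arm, or disappointment in the control arm) makes the programme look less effective. A negative δ (for example, apprehension about an extra session) makes it look more effective.

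**Size.** The article supplies neither δ nor k. The following is illustration only, under the assumptions δ = 0.05 to 0.20 SD and k = 0. The article states no effect size or SD, so a benchmark has to be back-calculated, assuming two-sided 5% and 90% power:

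- Full trial, 375 per arm: (1.960 + 1.282) × √(2/375) = 3.242 × 0.0730 = 0.237 SD.
- Pilot, 51 per arm: 3.242 × √(2/51) = 3.242 × 0.198 = 0.642 SD.

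Against the full-trial value, the assumed range is 0.05/0.237 = 21% to 0.20/0.237 = 84%. Against the pilot value it is 0.05/0.642 = 8% to 0.20/0.642 = 31%. The spread shows that any percentage here reflects the chosen shift and benchmark, and nothing the article establishes.

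**The case against.** The strongest reply is that the article never says patients hear the result before completing T1. It says the nurse makes a call and that baseline data follow. The statement on blinding concerns the type of intervention and gives no moment of disclosure. This stands as a limit: that patients know their arm at T1 is an inference. It does not rescue the text, because nothing withholds the result. If withholding is intended, the section needs to say so.

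Several stronger readings are tempting and are not supported:

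- *That T1 scores are used to judge the success of randomisation and any shift is then adjusted away.* The imbalance check in the Analysis section refers to medical, sociological and other baseline risk factors. It does not name T1 STAI, POMS or CASE scores. Only if those scores were also treated as baseline factors could a reaction to allocation be mistaken for chance imbalance.
- *That every baseline-adjusted estimate is biased.* No analysis adjusted for T1 scores is specified. The test-retest range of 0.65 to 0.86 given under Measures belongs to the STAI and cannot be carried over to POMS or CASE.
- *That a large fraction of the target effect is lost.* This needs an assumed shift that vanishes by follow-up, set against a back-calculated effect for the full trial, whereas the current proposal is a pilot of 51 per arm.
- *That disappointed patients will refuse the baseline form.* This is possible, but the article offers nothing to support it.

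One further point has some force. The Measures section names the trait version of the STAI, and a disposition is less likely than a state to move on hearing an allocation. That section is itself unclear about state versus trait, and POMS and CASE could still react.

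**Conclusion.** The concern holds as a flaw in the stated order of procedures. With T1 collected after the allocation call, from unblinded patients, by self-report on the outcome scales, and with no provision to withhold the result, T1 scores can already reflect the arm. The order is fixed explicitly in the article, so this is not a detail left to a fuller document.

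The consequence is conditional. It requires that patients learn the arm before completing T1, that they react to it, and that the reaction does not carry forward equally. The group-by-time contrast is then biased by the part not carried forward. The size and direction are unknown. A reader might infer that bias is established, or that most of the detectable effect is at risk; the article supports neither.

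It is still worth correcting before recruitment. The exposure is avoidable and cannot be undone after data collection, and the pilot exists to test the design and process intended for the larger trial.

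**What to change.** Reword the Allocation concealment/implementation section so that consent is followed by completion and return of all T1 questionnaires, and only then by the telephone call that releases the allocation. The independent contact can ask the nurse to confirm that the T1 forms have been handed in before giving the result. For consistency, the Data collection section can state that T1 is at recruitment and before allocation.

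The cost is small but not nil. Forms, staff and sample size are unchanged, and the call gains one confirmation step. Because the protocol already has ethics approval, a minor amendment may be needed.
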